Although multimodal EEG-fNIRS is considered to combine the advantages of EEG and fNIRS in a way that compensates for the limitations of each modality, its potential to record cerebral activity features has not been comprehensively investigated [26]. In motor rehabilitation, motor imagery (MI) – the mental representation of an action without its actual execution [42] – is commonly incorporated into NF protocols to target brain motor areas, making it a suitable task for anticipating later clinical application [9]. To our knowledge, no study has explored the effect of multimodal EEG-fNIRS-based NF in the context of MI. Thus, the aim of this paper is to evaluate the efficiency of EEG-fNIRS-based NF for MI in comparison to unimodal EEG-based and fNIRS-based NF. To reach this objective, we developed and implemented an experimental platform for multimodal EEG-fNIRS NF in the context of upper limb (UL) MI. Implementing such multimodal systems presents significant challenges, including the need for seamless coordination and synchronization of two inherently distinct systems, while maintaining real-time performance and ensuring that they do not interfere with each other. We then designed a randomized controlled study with healthy volunteers to assess the potential of multimodal EEG-fNIRS NF. We hypothesize that presenting participants with visual NF based on a combined score from both EEG and fNIRS signals will result in higher sensorimotor brain activity reflected in both EEG and fNIRS signals. As exploratory outcomes, we will investigate the participants’ feeling of NF control, the relationship between the motor imagery vividness (i.e., ability to build image and kinesthetic sensation of a movement) and the NF score. We will start by presenting the designed and already operational experimental platform and will then present the study protocol proposed to evaluate the effects of EEG-fNIRS based NF.

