#### 2.2.1. *Participants.*

Thirty healthy adults will be recruited. The inclusion criteria are i) 18-year-old or older, and ii) right-handed (score > 0.5 Edinburgh inventory, Oldfield, 1971 [61]). The non-inclusion criteria are i) to report a neurologic or psychiatric disease, ii) to report left upper limb (UL) orthopedic issues. All participants will have to read an information letter and sign an informed consent form before participating in the experiment.

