#### 2.2.5. *Statistical analysis.*

Statistical analysis will be performed using the latest version of the R software. A significance level of p < 0.05 will be used for all analyses. The primary outcome will be the difference in the brain activity between the three conditions: EEG-based NF, fNIRS-based NF and EEG-fNIRS-based NF. To check that the participant has succeeded, at least to some extent, in performing the neurofeedback task in each condition, we will study the NF scores. The exploratory outcomes will include the perception of control over the gauge and the strategies employed in relation to the NF condition as well as the link between the MI abilities and the performance at the NF-task. To assess the normality of the NF scores and brain activity data (i.e., EEG-ERD, EEG-ERS, fNIRS-HbR, fNIRS-HbO_2_), the Shapiro-Wilk test will be conducted. If the data are normally distributed, parametric repeated measures ANOVA will be used for mean comparisons. In cases where the data do not follow a normal distribution, non-parametric Friedman tests will be employed to evaluate differences among conditions. The perception of control over the gauge, as a function of the NF condition, will also be compared using the Friedman test. Lastly, as an exploratory analysis, Pearson correlation coefficient will be used to examine the relationship between the feeling of NF control, the MI abilities and the NF scores, depending on the NF condition.

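### The primary test asks only whether the three conditions differ, while the hypothesis is that combined NF beats each unimodal NF in both signals

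*Protocol article*

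**What the plan says.** The aim in section 1 (Background) is to "evaluate the efficiency of EEG-fNIRS-based NF for MI in comparison to unimodal EEG-based and fNIRS-based NF". The hypothesis in the same section is that feedback built on the combined score "will result in higher sensorimotor brain activity reflected in both EEG and fNIRS signals". Together these give a direction (higher), two comparators (EEG-NF and fNIRS-NF) and two signals in which the effect should appear.

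Section 2.2.5 (Statistical analysis) sets the primary analysis in other terms: "The primary outcome will be the difference in the brain activity between the three conditions". For normal data, "If the data are normally distributed, parametric repeated measures ANOVA will be used for mean comparisons"; otherwise, "non-parametric Friedman tests will be employed to evaluate differences among conditions". On the error rate it says: "A significance level of p < 0.05 will be used for all analyses".

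The section names no contrast of combined against unimodal NF, no direction and no rule for success. Its other analyses are a check on NF scores, a Friedman test on perceived control and exploratory correlations. None of them compares combined with unimodal NF on brain activity.

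**The concern.** A three-condition F or Friedman test has one alternative: the conditions are not all alike. Any departure counts, including EEG-NF differing from fNIRS-NF with no gain from combining them, or combined NF being the worst of the three. The primary result could therefore reach p < 0.05 while the data contradict the hypothesis, and a reader could take it as support for multimodal feedback.

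The design leaves room for this. The feedback follows only the EEG score in one condition, only the fNIRS score in another and their average in the third (section 2.1.3), so the two unimodal conditions could well differ on a given measure.

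**Working it through.** **Inputs from the article.** Thirty participants (section 2.2.1), three conditions within each participant (section 2.2.2), significance level 0.05 (section 2.2.5). The article gives no effect size, SD or power figure, so there is no stated figure to reproduce.

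**Assumed inputs.** Normal data, independent within-subject errors with SD 1, and condition means in units of that SD, as listed below.

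**Step 1: symmetry.** The ANOVA F statistic depends on the sum of squared deviations of the condition means from their overall mean. The Friedman statistic depends on the sum of squared rank totals. Exchanging labels or reversing the sign of the data changes neither sum. In a simulated data set, both p-values were identical after relabelling and after sign reversal (ANOVA 0.266, Friedman 0.648). This step needs no effect-size assumption.

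**Step 2: how often the ANOVA is significant.** The noncentrality is λ = n × Σ(μ_j − μ̄)² / σ², with 2 and (30 − 1) × (3 − 1) = 58 degrees of freedom.

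- Combined best by 0.7 (means 0, 0, +0.7): λ = 30 × 0.49 × 2/3 = 9.8.
- Combined worst by 0.7 (means 0, 0, −0.7): λ = 9.8 again.
- EEG-NF 0.8, combined 0.4, fNIRS-NF 0: λ = 30 × (0.16 + 0 + 0.16) = 9.6.
- EEG-NF 0.8, the other two 0: λ = 30 × 0.64 × 2/3 = 12.8.

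| True state | ANOVA p < 0.05 | Friedman p < 0.05 |
|---|---|---|
| Combined best by 0.7 | 78% | 65% |
| Combined worst by 0.7 | 78–79% | 65% |
| 0.8 / 0.4 / 0 | about 77% | 64% |
| 0.8 / 0 / 0 | 89% | 77% |

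In the third row, combined NF is significantly above EEG-NF in under 0.1% of trials.

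**Step 3: range over correlation.** Here the total SD is 1 and the shift is 0.5 of it. At within-subject correlation 0.3 / 0.5 / 0.7, the ANOVA is significant in 64% / 79% / 95% of trials with combined best and in 64% / 80% / 95% with combined worst. The corresponding Friedman rates are 52% / 66% / 88% and 51% / 66% / 87%. The differences are within simulation error.

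**Step 4: what contrasts deliver.** With combined best by 0.7, each paired difference has SD √2. The noncentrality of the paired t-test is 0.7/√2 × √30 = 2.71 on 29 degrees of freedom, which gives 74–75% power per contrast at two-sided 0.05. By simulation, both contrasts favour combined in about 61% of trials. With combined worst, or between the unimodal conditions as in the third row, both succeed in under 0.1%.

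If the same effect held on a second measure and both measures had to succeed, power would be about 0.61 × 0.61 = 37% with independent measures, rising towards 61% as they become more dependent.

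**The case against.** The strongest reply is that a condensed article need not list follow-up comparisons. Pairwise tests after a significant ANOVA or Friedman test are routine and may stand in an analysis plan that is not shown. The article also never says that the omnibus p-value alone decides the hypothesis. This stands in part: missing post hoc detail is not the point here. What the article does fix is a primary outcome without direction, and that conflicts with its own hypothesis. Unspecified follow-up tests would also leave open which contrasts count and whether one or all must succeed.

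Two stronger readings are tempting, and the document supports neither.

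- A reader might infer that EEG-NF is expected to lead on ERD and fNIRS-NF on HbO2, with combined NF between them. The article does not say so, and its hypothesis predicts the opposite. Participants are blinded to condition and imagine left-hand movements throughout, and section 3 assumes that the two signals are correlated. The 0.8 / 0.4 / 0 example shows a possibility only.
- A reader might infer that the study can neither confirm nor reject its hypothesis. That goes too far. EEG and fNIRS measures are kept separate and averaged by condition (section 2.2.4), so the means will show direction descriptively, and an unseen plan may hold follow-up comparisons.

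**Conclusion.** The primary analysis in section 2.2.5 does not match the hypothesis in section 1. It tests for any difference among three conditions, whereas the hypothesis is superiority of one condition over each of two others in two signals. The mismatch follows from the form of the tests and does not depend on the assumed effects. Those effects only show how often it could mislead: in the examples the ANOVA is significant in about 78% of trials whether the hypothesis is true or reversed. The percentages rest on 30 complete participants, normal data and the assumed means and error structure. Of the tests the article names, none supports a claim that combined NF is better than each unimodal condition.

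**What to change.** In section 2.2.5:

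1. Name one EEG and one fNIRS measure as primary, for example contralateral alpha ERD and contralateral ΔHbO2, the signals used for feedback. State the favourable direction of each; for the ERD ratio in section 2.1.3 this is the more negative value.
2. For each measure, pre-specify two paired contrasts, EEG-fNIRS minus EEG-NF and EEG-fNIRS minus fNIRS-NF, with estimate and 95% CI. Give a paired non-parametric counterpart for non-normal data.
3. State the success rule. If all four contrasts must favour EEG-fNIRS, as the hypothesis about both signals implies, each can be tested at 0.05 without adjustment. If one contrast or one measure would suffice, apply Holm across those that could carry the claim.
4. Keep the ANOVA or Friedman test as descriptive.
5. Date the change before condition-level data are examined. Section 2.2 says that acquisition started on 1 December 2024 and runs to 30 June 2025, so this is a documented change to a running study and more than an edit of wording.

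No new data or design change is needed. The cost is power, as shown in the working: about 61% for both contrasts on one measure against 78% for the omnibus test in the 0.7 SD example, and lower still if both measures are required. The higher figure belongs to a test that answers a different question.

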#### 2.2.6. *Data management plan.*

The participant will only be identified by a unique identification number. An identification list of subjects will be kept in the investigator’s file. The investigator will ensure that the anonymity of each person participating in the study is guaranteed. Information will be collected for each participant in a standardized observation booklet filled out by the investigator. The data will be stored on secure servers using the Shanoir web platform (https://project.inria.fr/shanoir/), which operates in compliance with the GDPR (i.e., General Data Protection Regulation of the European Union). If participant’s consent is withdrawn, the data already collected will be destroyed at the participant’s request. On the results paper of the study protocol, the de-identified data will be shared, in accordance with the ethic committee of the Inria laboratory (COERLE, Inria Operational Committee for the Assessment of Legal and Ethical Risk, nº 2024−27).

## 3. Discussion

The aim of this paper was to present the experimental platform developed for EEG-fNIRS-based NF and to propose a study protocol that will be conducted to evaluate the effects of multimodal EEG and fNIRS NF for MI of the left upper limb in comparison to unimodal EEG-NF and fNIRS-NF.

**Experimental platform for multimodal NF.** The design of the NF platform was based on prior work with EEG-NF [27,73,74,75] and existing literature on fNIRS-NF [22,23,52]. This platform relies on a modular architecture and offers the possibility of distributing the system on different processing units, providing either EEG only, fNIRS only or combined EEG-fNIRS scores. This paper proposes a methodology that addresses the technical challenge of integrating EEG and fNIRS systems for real-time brain activity analysis. The choice to combine both EEG and fNIRS information into a single neurofeedback (NF) stream was motivated by previous research showing that participants find it easier to control a single mixed feedback signal, rather than multiple separate signals [27]. Additionally, because the fNIRS hemodynamic response is delayed by a few s, presenting the signals separately could lead to reduced performance, as participants may focus on the faster-changing EEG feedback.

Positioning the fNIRS channels and EEG electrodes was crucial for our cap design as we aimed to record the EEG and fNIRS responses originating from the same cerebral location which implies an overlapping position for the EEG electrode and the fNIRS channels. For the rest of the cap, to optimize the set-up and its mobility, we privileged a maximal coverage of the pre-motor, sensorimotor and primary motor brain area for both EEG and fNIRS. The pre-processing steps and NF score extraction were designed in line with the literature [22,23,28,52,73,74,76]. To take into account extracerebral activity confound, we enhanced our pipeline through/with a real-time short channel correction. But one limitation here is to use only the ΔHbO_2_ signal as NF-fNIRS parameters without including ΔHbR in the score calculation [52]. This choice was made based on previous works where ΔHbO2 was used successfully to calculate changes in hemodynamic activity in the right-M1 in healthy young adults [77,78] and individuals with pathologies [79,80]. Moreover, according to the Hemodynamic Response Function (HRF), evoked changes in cerebral oxygenation, i.e., increased HBO_2_, reflect increased brain activity [48]. The HbR signal will be exploited together with the HbO2 signal for the offline analysis.

A technical test confirmed that our platform operates reliably (i.e., easy to use, without lags, recording all data points), and in particular that EEG and fNIRS signals can be acquired simultaneously and processed in real time to provide unimodal or multimodal NF scores.

**Study protocol to evaluate multimodal neurofeedback.** Our protocol will be the first trial to evaluate the impact of multimodal NF with EEG and fNIRS for upper-limb motor imagery. In this study, we will implement integrated NF requiring participants to regulate both EEG and fNIRS simultaneously to reach the NF target. This approach assumes that both signals can be combined since neurovascular studies demonstrate a correlation between electrophysiological (EEG) and hemodynamic (fNIRS) activity [81]. What makes multimodality particularly interesting is that these methods provide complementary information regarding brain functional activity during upper limb movements [80,82,83]. Both EEG-based NF (EEG-NF) and fNIRS-based NF (fNIRS-NF) have been explored separately in both healthy and clinical contexts (for reviews on EEG, see [84–86] Viviani & Vallesi, 2021; Patil et al., 2023; Cheng et al., 2024; for reviews on fNIRS, see [22,52,87]. As in Godet et al. (2023) [49], we followed the CRED-checklist [66] and NF recommendations for the design of the protocol and its evaluation with for instance the questions asked to the participants at the end of each condition about the strategies and feeling of control. To optimize the system, the use of MRI or neuro-navigation system would be beneficial to locate the brain regions of interest. With our current system, will only use the 10−10 international system reference, which could lead to lower spatial accuracy. Since all sensors are set upon the same layout, it will not be possible to cover exactly the same brain areas with the EEG and fNIRS, but for NF robustness, we designed the cap to cover exactly the same brain area for the NF target. This was achieved by putting the EEG C4 channel in the middle of 2 sources and 2 detectors. A compromise needs to be made when implementing EEG and fNIRS for real-time applications, due to the difference in temporal resolution between the two modalities. Indeed, the frequency of the fNIRS score calculation is lower than that of the EEG, in line with the temporal dynamics of fNIRS and EEG (neurovascular response or electrical response respectively). However, this was done in order to get the best out of both systems, without refreshing the EEG too often, so that the NF is not mainly guided by it, and with a slightly higher refreshing frequency of the fNIRS, to take advantage of its resolution.

Finally, the design of the NF protocols plays a critical role in shaping the underlying neural mechanisms that support learning and plasticity. NF is thought to promote plastic changes through repeated, reinforced activation of specific brain circuits, consistent with principles of operant conditioning and Hebbian learning [3,88]. In our study protocol, we chose a block design in order to facilitate stronger and more consistent activation of targeted neural networks over time, promoting experience-dependent synaptic modification and functional reorganization [2]. This block design, coupled with real-time feedback and repeated training, creates the conditions for neural adaptation and learning, even if the exact causal pathways remain an active area of investigation [3].

The designed protocol aims to achieve an increased brain activity in the right primary motor cortex, the participants being instructed to mentally simulate left hand movement. Nevertheless, as the strategy used will only be subjectively reported, we will not be able to really track if the strategy might change from block to block and the subjective report will not necessarily refer to the whole condition. The reporting strategies will nevertheless give us a general idea of the most successful strategy used, and via the quality of the MI (using KVIQ scale, [67]), we will be able to see if participants feel they have mastered mental movement simulation.

**Perspectives for clinical applications.** With the potential to enhance neuroplasticity, such EEG-fNIRS-NF system could have significant applications in clinical settings, particularly in motor and brain rehabilitation. A deeper understanding of its benefits could be achieved by examining neurovascular coupling (NVC). Indeed, altered NVC is common after stroke, making its assessment highly relevant for interventions aimed at stimulating neuroplasticity and thus motor recovery. NVC describes the interaction between electrical neural activity (excitatory or inhibitory), cerebral blood flow (hemodynamic responses), and the brain’s metabolic energy consumption [89]. This coupling leads to hemodynamic changes in brain regions that reflect electrical activity, characterized by a localized increase in blood flow [90]. As such, NVC is essential for understanding brain function and dysfunction. In this context, combining EEG and fNIRS has been shown to be particularly effective for elucidating NVC processes in humans [82]. Since both EEG and fNIRS can be recorded simultaneously without interfering with one another (i.e., not degrading one signal or the other, as in EEG-fMRI, Ihalainen et al., 2015 [91]), they offer complementary insights into electrical and hemodynamic brain activities at improved resolution [41,92]. Such a platform could be easily implemented in clinical practice. Recent decades, fNIRS and EEG methods have been used in several stroke studies [93]. This relies on providing an accessible, affordable system, robust, easy to install and use – what we had in mind when developing the software. Our future findings could come to reinforce their interest, especially when associated with functional evaluation. A long-term objective of this study would be to explore the impact of this multimodal system on post-stroke rehabilitation, building on previous findings that demonstrate the motor recovery benefits of neurofeedback methods [9].

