**Fig 2 pone.0331177.g002:**
[figure not shown]
Epoching of the EEG and fNIRS signals. 1-A represents the epochs averaged for the rest period and 1-B for the task for the EEG signal. 2-A represents the epochs averaged for the rest period and 2-B for the NF task for the fNIRS signal.

$Ratio\;ERD=\frac{\left(pTask\;-pRest\right)}{pRest}*100$, where *pRest* represents the power averaged from the epochs from the last 5 s of the preceding rest period and *pTask* represents the power averaged from the last 1.5 s that capture the near-instantaneous power during the NF task [53]. A new ERD ratio is calculated every time a new epoch is received (i.e., every 0.25 s according to the time based epoching). During the calibration session, the 30th percentile of the ERD ratios is extracted from all the calibration blocks and set as the target level to reach 100% during the NF session. This choice was made based on previous NF protocols, in order to individually set the difficulty of the NF task (i.e., maximal value of the gauge). We chose to focus solely on the expected movement-related desynchronization, which is indicated by a negative ERD during the task [54]. This value is stored and used to compute the EEG-NF score: $NF_{EEG}=\;\frac{Ratio\;ERD\;(NF\;task)}{Ratio\;ERD\;(calibration)}*100$.

**fNIRS**-**NF score.** A time-based epoching is applied to generate epochs of 0.96 s every 0.48 s for the fNIRS (see Fig 3). The duration of the epochs and moving window of the fNIRS is based on the sampling frequency (i.e., 6.25 Hz), ensuring a constant and integer number of fNIRS samples across all epochs. A fNIRS NF score is calculated every 0.48 s based on 1.92 s periods (i.e., averaged of 3 epochs) using a 4.8 s rest periods (i.e., average of 9 epochs, see Fig 2). In order to prevent from temporal drift, the fNIRS-NF score is computed considering the last 4.8* seconds of the previous rest period as the baseline. The **diff*Δ*HbO**_*2*_ is then calculated as followed:

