**Fig 3 pone.0331177.g003:**
[figure not shown]
Implementation of EEG and fNIRS from acquisition and real-time preprocessing of EEG and fNIRS signals to the calculation of the NF score. 1. Acquisition is done through the OpenViBE acquisition server for the EEG, and for the fNIRS the raw signal is recorded via the NIRStar software and transferred to the openViBE acquisition software via LSL communication. 2. Real-time preprocessing steps are conducted in the OpenViBE designer software.

**diff*Δ*HBO**_*2*_* = ΔHBO*_*2(Task)*_
**-* Δ*HBO**_*2(Rest*)_*,* where *ΔHBO*_*2(Rest)*_ represents the average of the epochs from the last 4.8 s of the preceding rest period and *ΔHbO*_*2(Task)*_ represents the average over the last 1.92 s reflecting the near-instantaneous relative variation in oxyhemoglobin concentration during the NF [49]. A new ΔHbO_2_ value will be calculated every 0.48 s. To follow the EEG targets, during the calibration session, the 30th percentile of the positive ΔHbO_2_ values as the target level to reach 100% during the NF session. This value will be stored and used to compute the fNIRS NF score:

$$\;NF_{fNIRS}\;=\;\frac{diff\Delta HBO_{2}\;(NF\;task)}{diff\Delta HBO_{2}\;(calibration)}*100.$$

We focus specifically on the expected response during movement, an increase in the relative ΔHBO_2_ concentration during the task is expected, which is reflected by a positive ΔHbO_2_ [55].

**EEG-fNIRS-NF score.** The EEG-fNIRS combined score is based on the average of the *NF*_*EEG*_ and *NF*_*fNIRS*_ scores. It is refreshed every time a new EEG or fNIRS score is calculated:

$$NF_{EEG\text{-}fNIRS}\;=\;\frac{{NF}_{EEG}+{NF}_{fNIRS}}{2}.$$

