**Neurofeedback score metaphor.** The implementation of the score metaphor is presented on Fig 4. We chose a visual feedback adapted from the work of Perronnet et al. (2020) [28]. The NF paradigm includes the use of a visual metaphor consisting of a vertical gauge with a yellow ball moving up and down in 1D. The ball position represents the EEG scores, fNIRS scores or the average of both EEG and fNIRS scores. The background of the 1D gauge is divided into four regions to provide the subject with reference points. The NF score calculation is carried out using a dedicated Python code (Python 3.12). Visual instructions and feedback are presented to the user using the PsychoPy toolbox (Peirce et al., 2019, version 2023.2.3 [60]). The ball position ranges from 0% to 100%. If the NF score exceeds 100%, it is capped at 100%, and if it is negative, it is set to 0%. Both the *NF*_*EEG*_ and *NF*_*fNIRS*_ score is transmitted to the Python Psychopy script through LSL and the ball position is updated accordingly. Every time a new score arrives, the ball position is updated.

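### As the formulas read, one modality can fill the combined gauge alone, so the combined condition does not require regulation of both EEG and fNIRS

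*Protocol article*

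**What the plan says.** All places are in the protocol article.

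- **Claim** (3. Discussion, on the study protocol): "we will implement integrated NF requiring participants to regulate both EEG and fNIRS simultaneously to reach the NF target".
- **Combined score** (2.1.3): "The EEG-fNIRS combined score is based on the average of the" EEG and fNIRS scores, that is, half their sum. No minimum per modality is set.
- **EEG target** (2.1.3): "the 30th percentile of the ERD ratios is extracted from all the calibration blocks and set as the target level to reach 100" per cent. NF_EEG is the task ERD ratio divided by this value, times 100.
- **fNIRS target** (2.1.3): "the 30th percentile of the positive ΔHbO_2_ values as the target level to reach 100% during the NF session". NF_fNIRS is the task difference in HbO2 divided by the calibration value, times 100.
- **Display** (2.1.4): "The ball position represents the EEG scores, fNIRS scores or the average of both EEG and fNIRS scores". The limit follows in the same paragraph: "If the NF score exceeds 100%, it is capped at 100%, and if it is negative, it is set to 0" per cent. No separate limit on either component before averaging is stated.
- **Use of the scores**: section 2.2.4 stores NF_EEG, NF_fNIRS and the combined score by condition and run, averages them within a run and extracts their time courses. Section 2.2.5 uses the NF scores to check that participants achieved some success in each condition. It names the difference in brain activity between conditions as the primary outcome.

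**The concern.** A mean is compensatory: a surplus in one term makes up for a deficit in the other. If the terms are not limited first, a participant can reach the target with one signal flat or moving the wrong way. The Discussion then claims a property that the scoring rule lacks.

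Two things are at stake. First, the description of the combined condition: readers would take a full gauge as evidence of joint regulation. Second, the success check: a run average of 100 on the combined score is compatible with 100 on both components, but also with 0 on one and 200 on the other.

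**Working it through.** The article gives no figure to reproduce here, so the check evaluates its own formulas.

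**1. Two orders of operation.** Let clip(x) limit x to 0-100.

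- A, as the text reads: display = clip((NF_EEG + NF_fNIRS)/2)
- B, the alternative: display = (clip(NF_EEG) + clip(NF_fNIRS))/2

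| NF_EEG | NF_fNIRS | A | B |
|---|---|---|---|
| 100 | 100 | 100 | 100 |
| 150 | 50 | 100 | 75 |
| 200 | 0 | 100 | 50 |
| 0 | 200 | 100 | 50 |
| -50 | 250 | 100 | 50 |

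Under B the display reaches 100% only when both components are at 100 or more. Under A it does not need both.

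**2. Can each modality do it alone?** With the other component at 0, a modality needs a score of 200.

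- *EEG.* The ERD ratio, (pTask - pRest)/pRest x 100, cannot fall below -100%. With calibration target T (negative), the largest NF_EEG is (100/|T|) x 100. Requiring at least 200 gives |T| <= 50. For T = -30% the maximum is 333; for T = -60% it is 167, and the combined score is then at most 167/2 = 83%.
- *fNIRS.* The numerator is a concentration difference with no upper limit in the formula, so 200 is always possible in principle.

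**3. How often? Illustration only.** The article gives no signal distributions, so all of the following is assumed.

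- Take HbO2 differences as N(mu, 1), the same in calibration and task. The 30th percentile of the positive values is 0.385, 0.540 and 0.775 for mu = 0, 0.5 and 1. The share of all values at or above twice that is 22%, 28% and 29%.
- Add an independent EEG signal: lognormal power ratio, ERD mean -10% with SD 30 or mean -20% with SD 25. The gauge is full in 28-47% of updates under A and 10-18% under B. Of the full-gauge updates under A, 59-65% have at least one component below its own target, but only 7-16% have one component at or below 0.
- With ERD drawn from a normal distribution instead, the share with one component at or below 0 is 9-21% when the signals are independent. It falls to 5-12% at a correlation of 0.3 between the two scores, and to 1-5% at 0.6. The share with one component below target falls to 50-55% and 40-46%.

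Steps 1 and 2 are algebra and need none of these assumptions. Step 3 shows that the frequency runs from about 1% to 21% for the strict case of one component at or below 0, depending mainly on the correlation.

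**The case against.** **The order is not explicit.** Section 2.1.3 also uses the term NF score for each component, and section 2.1.4 says both component scores are sent to the display script, so each could be capped there. This stands as a possibility. If the code caps first, 100% does require both and the contradiction disappears; sections 2.1.3 and 2.1.4 would then need to state that step. Averaging first remains the more direct reading, because the equation uses the unlimited components and the limit sits in the description of the ball.

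**Stronger readings that the article does not support.**

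- A reader might infer that the planned intervention is not delivered, or that the combined condition is in effect fNIRS feedback with EEG noise. But the hypothesis in section 1 concerns feedback on a combined score from both signals, and that is delivered. Only the Discussion sentence claims more. How far fNIRS dominates cannot be known without the signal distributions.
- A reader might infer that no result could be attributed to joint regulation. But the primary outcome is brain activity, processed offline from both modalities in every condition (2.2.4) and not calculated from the combined score. The stored component scores also allow joint regulation to be examined directly.
- A reader might take the 59-65% as the rate of single-modality success. It is not: it counts cases such as (120, 80), where both signals are regulated.

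**Capping first has its own cost.** If task values match calibration, EEG alone is at 100% in 30% of updates by definition of its target, and fNIRS alone in 35-59% (mu from 0 to 1). Averaging first gives 28-47%, roughly comparable; capping first gives 10-18%. The combined gauge would then be much harder than both comparators. This objection stands and shapes the fix.

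**Conclusion.** The point holds as an inconsistency between the Discussion and sections 2.1.3 and 2.1.4, on the reading that averaging precedes capping. One modality at 200% of its target fills the gauge with the other at zero; this is open to fNIRS without limit and to EEG only for targets no stronger than -50% ERD. It follows that a high combined score is not evidence of success in both modalities for the check in section 2.2.5. The frequency is unknown, and the percentages above are illustrations under assumed distributions. The primary comparison of brain activity is not itself miscalculated. What is affected is the description of the combined condition and what its score can be taken to show.

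**What to change.** 1. State in sections 2.1.3 and 2.1.4 whether NF_EEG and NF_fNIRS are limited to 0-100 before or after averaging, as the code does it.
2. If they are not limited first, replace the Discussion claim with wording such as *feedback based on the average of both signals*.
3. In the combined condition, base the success check on NF_EEG and NF_fNIRS separately, and report the share of full-gauge time in which both were at or above their own targets.

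The cost is a few sentences and one descriptive table. The component scores and time courses are already to be stored (2.2.4), so no new data are needed.

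Limiting each component before averaging would enforce the stated property, with one signal alone then giving at most 50%. Because it makes the combined gauge harder than the unimodal ones, it suits a future study or a documented change. With acquisition scheduled from 1 December 2024 to 30 June 2025, an unmarked switch partway would mix two feedback rules within one condition.
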